## Abstract

Background: Pressure injuries (PIs) represent a significant healthcare challenge in Singapore among the aging population. These injuries contribute to increased morbidity, mortality, and healthcare expenditure. Existing research predominantly explores single-component interventions in hospital environments, often yielding limited success. The INCA Trial aims to address this research gap by conducting a comprehensive, cluster randomized controlled trial that integrates education, individualized nutritional support, and community nursing care. This study is designed to evaluate clinical and cost-effectiveness outcomes, focusing on PI wound area reduction and incremental costs associated with the intervention. Methods: The INCA Trial employs a two-group, non-blinded, cluster randomized, and pragmatic clinical trial design, recruiting 380 adult individuals (age ≥ 21 years) living in the community with stage II, III, IV, and unstageable PI(s) who are receiving home nursing service in Singapore. Cluster randomization is stratified by postal codes to minimize treatment contamination. The intervention arm will receive an individualized nutrition and nursing care bundle (dietary education with nutritional supplementation), while the control arm will receive standard care. The 90-day intervention will be followed by outcome assessments extending over one year. Primary outcomes include changes in PI wound area and the proportion of participants achieving a ≥40% area reduction. Secondary outcomes include health-related quality of life (HRQOL), nutritional status, and hospitalization rates. Data analysis will be conducted on an intention-to-treat (ITT) basis, supplemented by interim analyses for efficacy and futility and pre-specified sensitivity and subgroup analyses. The primary outcome for the cost-effectiveness analysis will be based on the change to total costs compared to the change to health benefits, as measured by quality-adjusted life years (QALYs). Discussion: The INCA Trial serves as a pioneering effort in its approach to PI management in community settings. This study uniquely emphasizes both clinical and economic outcomes and melds education, intensive dietetic support, and community nursing care for a holistic approach to enhancing PI management.

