### 2.4. Sample Size Estimation

The sample size calculation is based on the results reported by Cereda et al. [17], where an odds ratio (OR) of 2.0 for ≥ 40% improvement in wound area on patients receiving a specialized nutritional supplementation containing arginine is used. To have 80% power to detect this difference with a 2-tailed type I error of less than 5%, we require at least 144 subjects per arm. After assuming a 20% mortality and 10% withdrawal rate (based on a Cereda et al. [17] study of 16% mortality and 6% withdrawal and a Chaboyer et al. [22] study of 8% loss to follow-up), we plan to enroll a total of 380 subjects (190 per arm). As we will be undertaking an intention-to-treat (ITT) analysis, anticipated adherence will be one of the outcome measurements to determine if the intervention (education and supplementation) is acceptable to the participants (Supplementary Material Figure S1).

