### 5.1. Outcome Measures

Dichotomous Outcomes: The frequency of outcomes will be determined, and we will utilize time-to-event analyses. The hazard ratios (HRs) along with their 95% confidence intervals (CIs) will be determined using a stratified Cox proportional hazards model.Continuous Outcomes: The differences between the intervention and control groups, along with their 95% CIs and corresponding *p*-values, will be documented.

Both patient-level and cluster-level data will be analyzed. We will address any imbalances in individual data by adjusting statistically using a mixed-effects Cox regression model performed by a statistician blinded to the group allocation. 

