### 5.2. Sensitivity Analyses

To ensure the robustness of our findings, sensitivity analyses will be conducted. Estimates will be adjusted considering pre-specified factors derived from the literature or known PI risk factors, such as age, BMI, nutritional status, wound severity, comorbidities, and socioeconomic status.

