## Figures and Tables

**Table 1 nutrients-16-00299-t001:** Exclusion criteria for the INCA Trial.

	Exclusion Criteria
1.	Septicaemia.
2.	Poorly controlled diabetes (*glycated hemoglobin level > 8.5%)* [20,26].
3.	Consumption of supplements will lead to fluid intake in excess of fluid restriction for the following conditions: Advanced renal disease not on dialysis (KDIGO [21,22] Stage G4 with an eGFR of 15–29 mL/min/1.73 m^2^ and Stage G5 with an eGFR of less than 15 mL/min/1.73 m^2^); Heart failure with reduced ejection fraction [27]; Advanced decompensated alcoholic and non-alcoholic liver cirrhosis [28,29].
4.	Current neoplastic disease or last chemotherapy or radiotherapy less than one year ago.
5.	Currently on immunosuppressive therapy.
6.	Palliative with *a lifespan of ≤ 3 months.*
7.	Known allergy reaction to L-arginine or phenylketonuria.
8.	Presence of an infected wound *(if it is the only pressure injury present on the participant).*
9.	Untreated diagnosed osteomyelitis [18,19,30,31,32].
10.	Pregnant women and children (there is limited evidence on the use of arginine in these groups).

**Table 2 nutrients-16-00299-t002:** Outcomes and the methods of measurement to be used in the cluster RCT.

Type	Outcome	Outcome Description	Measurement Method	Data Collection Time Point (t) and Time Frame	Performed by
Primary	Wound	Change in the area of pressure injury (cm^2^) from the baseline	Assessed by the change in wound area ^#^ from the baseline to the follow-up time points and measured with a 3D wound imaging device at the time of follow-up.	t_0_ baseline, t_1_ 30 days, t_1_ 60 days, t_3_ 90 days, t_4_ 6 months, and t_x_ 1 year Time frame: 1 year	Nurse
		The proportion of participants with ≥40% area reduction	Assessed by the number of participants with wound area ^#^ reduction ≥ 40% at the time of follow-up versus the baseline.	t_1_ 30 days, t_1_ 60 days, t_3_ 90 days, t_4_ 6 months, and t_x_ 1 year Time frame: 1 year	Nurse, CRC
Secondary	Wound	The proportion of participants with complete wound healing of the main wound	Assessed by the number of participants with complete healing of a wound ^#^, determined by clinical assessment and pressure injury staging.	t_1_ 30 days, t_1_ 60 days, t_3_ 90, t_4_ 6 months days, and t_x_ 1 year Time frame: 1 year	Nurse, CRC

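### The stratified Cox model named for the ≥40% area-reduction co-primary does not account for the randomised postal codes, and its hazard ratio is not the quantity that was defined and powered

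*Protocol article*

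**What the plan says.** Section 2.5 allocates postal codes 1:1, so everyone in a postal code is in the same arm. The Abstract puts it as "Cluster randomization is stratified by postal codes to minimize treatment contamination".

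Section 3.1 names two primary outcomes: change in wound area, and the proportion with at least a 40% reduction. Table 2 defines the second by counting participants with a wound area "reduction ≥ 40% at the time of follow-up versus the baseline", at each of five follow-up visits from 30 days to 1 year. Section 2.4 sizes the trial on "an odds ratio (OR) of 2.0 for ≥ 40% improvement in wound area".

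Section 5.1 then says three things about models:

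- Dichotomous outcomes are analysed as time to event, and hazard ratios "will be determined using a stratified Cox proportional hazards model". The strata are not named.
- For continuous outcomes, "The differences between the intervention and control groups, along with their 95% CIs" and p-values will be reported. No model is named.
- Patient-level and cluster-level data will both be analysed, and "We will address any imbalances in individual data by adjusting statistically using a mixed-effects Cox regression model". The random effect is not named.

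Section 5.2 brings in covariates, including wound severity, as a sensitivity analysis: "Estimates will be adjusted considering pre-specified factors derived from the literature or known PI risk factors".

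**The concern.** In a cluster-randomised trial the treatment contrast lies between clusters, so the primary model has to carry the between-cluster variance. Stratifying a Cox model does not do that. It gives each stratum its own baseline hazard and compares only within strata. A mixed-effects model could do it, but the one named is given a different purpose and is a survival model, so it cannot serve the continuous co-primary.

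There is also a mismatch of quantity. A proportion at a visit, summarised by an odds ratio, is not the same as time to reaching a 40% reduction, summarised by a hazard ratio. Wound area can increase again, so a wound that crosses 40% at day 30 and has re-expanded by day 90 is an event in the time-to-event analysis but not a responder at day 90.

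At stake are the type I error of the primary test and whether the reported effect can be compared with the one the trial was designed to detect.

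**Working it through.** **The plan's own figure.** Section 2.4 gives 144 evaluable per arm for OR 2.0, 80% power and two-sided 5%. The control response rate is not stated, so it has to be assumed. At 0.40 the intervention odds are 2 × 0.40/0.60 = 1.333, so the intervention rate is 0.571. The pooled two-proportion formula then gives about 132 per arm uncorrected and 144 with continuity correction. Across control rates of 0.333 to 0.50 the corrected formula gives about 144 to 148. The figure is therefore attainable, and it matches individual randomisation with no design effect.

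**Stratified Cox model and clusters.** The information on treatment in a stratified Cox model is the sum, over events, of the variance of the treatment indicator among those at risk in the same stratum.

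- Strata = randomised postal codes: the indicator is constant in every stratum, each variance is 0, and the total information is 0 (confirmed numerically). No hazard ratio exists.
- Strata = anything else, such as two broad locality groups each containing both arms: the hazard ratio is estimable, but the usual standard error treats people in the same postal code as independent.

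**Size of the test if clusters are ignored.** Inputs: 288 evaluable (2 × 144); k clusters, at most 82 from Section 2.2; mean size m = 288/k; ICC assumed. Design effect DE = 1 + (m − 1) × ICC. True size = 2 × [1 − Φ(1.96/√DE)].

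| Clusters | m | ICC | DE | True size | Power at 144 per arm, clusters handled | n per arm to keep power |
|---|---|---|---|---|---|---|
| 82 | 3.51 | 0.01 | 1.025 | 5.3% | 82% | 148 |
| 82 | 3.51 | 0.05 | 1.126 | 6.5% | 79% | 163 |
| 82 | 3.51 | 0.10 | 1.251 | 8.0% | 74% | 181 |
| 28 | 10.29 | 0.01 | 1.093 | 6.1% | 80% | 158 |
| 28 | 10.29 | 0.05 | 1.464 | 10.5% | 67% | 211 |
| 28 | 10.29 | 0.10 | 1.929 | 15.8% | 56% | 278 |

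Power is at a control rate of 0.40, where it is 83% with no clustering. The 28-cluster rows are illustrative: 28 is the number of districts, and Section 2.5 lets postal codes be excluded or combined.

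These rows assume equal cluster sizes. Simulating a two-proportion test with unequal sizes (coefficient of variation 0.6 in the run with the higher figures) and 266 analysed (380 × 0.70) gave, for 82 clusters, 5.6 to 6.8%, 7.2 to 7.7% and 9.3 to 10.6% at ICC 0.02, 0.05 and 0.10. That is the source of the upper end of 5 to 11%.

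An unclustered Cox test was also simulated directly, with 288 people, events recorded at 30, 60 and 90 days, and 800 replicates. With log-hazard cluster variances of 0.10 and 0.25 its size was about 7% and 7% (82 clusters) and 10% and 18% (28 clusters), against 5.1% with no clustering.

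**Odds ratio against hazard ratio.** Under proportional hazards, HR = ln(1 − p₂)/ln(1 − p₁). At p₁ = 0.50, p₂ = 0.667 and HR = 1.58. Over p₁ = 0.30 to 0.55 an OR of 2.0 corresponds to an HR of 1.74 to 1.55. With 144(p₁ + p₂) events, Schoenfeld power is 82 to 85%, clusters ignored.

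**Baseline area.** Variance is 2σ²(1 − ρ) for a change score and σ²(1 − ρ²) with baseline as covariate, a ratio of (1 + ρ)/2. That is 0.65 at ρ = 0.3 and 0.95 at ρ = 0.9, with ρ assumed.

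**The case against.** The best defence is that Section 5.1 is condensed, not wrong. It promises an analysis of cluster-level data, which is not limited to dichotomous outcomes and could cover wound area, and it names a mixed-effects model that could carry a random effect for postal code. The Cox strata are not stated, and Section 2.5 can be read as forming two locality groups before postal codes are allocated. The fuller analysis plan may settle all this.

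Part of that stands. Because the strata are unnamed, a reader might infer that the primary model gives no estimate at all; that holds on only one reading. A reader might also infer that wound area will be compared by an unadjusted mean difference. The text names no model for continuous outcomes, and silence is not a decision. Likewise Section 5.1 does not say that deaths are censored for wound response, and that detail is commonly left to the analysis plan. Nor can it be said that recruitment will produce imbalance: Section 2.5 states that allocation is concealed until participation is confirmed.

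What does not stand is that the remaining text repairs the named model. The mixed-effects model is tied to individual imbalance and not to the randomised unit, neither Cox model is designated primary, and no cluster method is attached to either co-primary. The odds-ratio and hazard-ratio statements conflict within the document whatever a later plan says.

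**Conclusion.** The point holds in this form: the model named for the dichotomous co-primary does not account for the randomised clusters on any reading of its strata, it is not reconciled with the second Cox model, and it targets a different quantity from the one defined in Table 2 and powered in Section 2.4.

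An inflated type I error follows only if clustering is in fact ignored. It would then be modest at the documented maximum of 82 postal codes and larger if fewer are used. The size rests on assumed ICCs and cluster counts.

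Two stronger readings are not supported. The odds-ratio and hazard-ratio mismatch does not weaken the test, since power for the corresponding hazard ratio is at or slightly above the planned 80%. Leaving baseline area out of the stated models is not an error: the endpoint is already change from baseline, a change score is valid, and wound severity is among the sensitivity covariates. Adjusting for baseline area is a gain in precision.

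**What to change.** In Section 5.1, replace the general model statements with one primary model per co-primary:

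- **≥40% reduction:** logistic regression at one visit that the sponsor designates, reporting an odds ratio, with a random intercept for the randomised unit. GEE with a small-sample correction is an alternative. State whether the odds ratio is cluster-specific or population-averaged.
- **Wound area:** a linear mixed model over the visits, with baseline area as covariate and a random intercept for the randomised unit.

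List the covariates for both models in advance so that adjustment does not depend on observed imbalance. Keep a Cox model with a cluster frailty for true time-to-event outcomes such as mortality, unplanned admission and time to healing. Remove the stratified Cox model for wound response, or name its strata and its role.

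The cost is wording in Sections 5.1 and 5.2; baseline area, stage, age and nutritional status are already collected. The real downside is that intervals widen for clustering, so effective power is below what the individually randomised calculation implies: at a control rate of 0.40, 74 to 82% instead of 83% with 82 clusters, under the assumed ICCs. Baseline adjustment may recover some precision for area.

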### 5.2. Sensitivity Analyses

To ensure the robustness of our findings, sensitivity analyses will be conducted. Estimates will be adjusted considering pre-specified factors derived from the literature or known PI risk factors, such as age, BMI, nutritional status, wound severity, comorbidities, and socioeconomic status.

### 5.3. Subgroup Analyses

A planned subgroup analysis will be performed by targeting specific nutritional status and intake variables, route of intake (oral versus enteral), staging of PIs, gender, age group, compliance to intervention, and functional status. 

### 5.4. Secondary Analyses

Per-protocol analyses planned include the proportion of wounds that will be executed, excluding subjects who:Suffer from wound infections;Show non-compliance to the treatment;Dropout from the trial;Die during the trial period.

### 5.5. Interim Analyses

We intend to conduct interim analyses for efficacy and futility when data are finalized for subsets of 100 and 200 subjects. Based on these interim findings, we might reassess our sample size to maintain the power required to detect a significant difference in the primary outcome between our two study groups. Sample size re-estimation may be performed to evaluate the power to detect a statistically significance difference in primary outcome between the intervention group and the control group based on an interim analysis. 

## 6. Economic Evaluation Protocol and Analytic Plans

As part of the research, a planned micro-costing study and cost-effectiveness analysis (CEA) alongside the cluster randomized controlled trial will be undertaken from the payer and healthcare system perspective. The economic evaluation protocol is developed in accordance with the CHEERS 2022 (Consolidated Health Economic Evaluation Reporting Standards 2022) [36] and international cost-effectiveness analysis guidelines [37,38,39].

### 6.1. Micro-Costing 

Micro-costing will be performed on a subsample of participants (n = 40; 10% of the sample population) over a 4-week period to supplement cost data for the CEA. This sample size will be 10% of the trial cohort and is deemed sufficient to represent the mean and distribution of resource use in the study population. Detailed data on resource use related to intervention will be collected by the home care nurses and research dietitians. We will only include direct costs for the micro-costing; that is, the resources directly consumed in the treatment (Supplementary Material). 

### 6.2. Cost-Effectiveness Analysis 

The primary outcome will be based on an intention-to-treat (ITT) principle for the CEA. The change to total costs will be compared to the change to health benefits, as measured by quality-adjusted life years (QALYs). Total costs will be estimated by considering the extra costs of the intervention and the change to the use of health services in subsequent time periods. QALY outcomes will be estimated using data from the EQ5D-5L, and the change due to the intervention will be estimated. Uncertainty will be included in probabilistic sensitivity analysis.

The incremental mean costs will be estimated from participants in both groups based on resource unit cost multiplied by resource utilization. The change to total costs and QALYs will be considered on the cost-effectiveness plane and analyzed quantitatively to estimate the probability that the adoption of intervention is a good decision against maximum willingness to pay thresholds for marginal health benefits, such as QALYs. Further details of the economic evaluation protocol are available in the Supplementary Material.

## 7. Trial Status

Recruitment started in October 2023.

## 8. Data Collection and Management

### 8.1. Data Collection 

Data will be collected by the nurses (for both groups) and the research dietitian (for the intervention group only) during each planned visit (Table 2). This will be carried out at the baseline, 30 days, 60 days, 90 days, and 12 months for the wound and nutritional data, hospital admissions, mortality, and health-related quality of life (HRQOL). The study schedule of enrolment, interventions, and assessments follows the recommendations from the SPIRIT statement [23] and the SPIRIT-OUTCOMES extension [24], as shown in Table 3.

### 8.2. Data Management

Data collected during the research will be kept strictly confidential and accessed only by delegated research team members. Data collected will be delinked, coded, and de-identified. Only de-identified data will be sent to the statistician for statistical analysis and to the health economist for economic evaluation. The data will be kept for three [3] years post-completion of the trial and will be destroyed and deleted subsequently. Methods may include overwriting data with a series of characters or reformatting the disk (destroying everything on it). If unable to overwrite data, we will consider pulverizing the hard disk to destroy hard disk data based on existing institutional research board guidelines.

### 8.3. Management and Safety

The investigator(s)/institution(s) will permit study-related monitoring, audits, and/or Centralised Institutional Review Board (CIRB) review and regulatory inspection(s), providing direct access to source data/documents to ensure compliance with the relevant data protection legislation. A combination of paper and electronic data will be collected for this study. All data recorded on paper will be handled, transferred, and stored securely. Paper data will be stored in the investigator site file for the duration of the study in a locked cupboard in a locked room. Data from paper records will be uploaded digitally by a delegated member of the local research team. No personal identifiers will be collected in study questionnaires.

Only related severe adverse events (SAEs) will be reported to the CIRB. Related means there is a reasonable possibility that the event may have been caused by participation in the research. The investigator is responsible for informing the CIRB after first knowledge that the case qualifies for reporting. Follow-up information will be actively sought and submitted as it becomes available. Related adverse events (AEs) will not be reported to the CIRB. However, the investigator is responsible for keeping a record of AE cases in the study site file.

We will provide an identification and description of individuals responsible for monitoring the trial, their roles, qualifications, and the frequency of the monitoring activities. We will also include a description of any specific events that would preclude a participant from continuing the intervention. The potential risks and the measures in place to protect participants against foreseeable risks are presented in the Participant Information Sheet and Consent form (Supplementary Material). 

Mechanisms are in place to protect subject privacy (e.g., interviews will take place in a private room, and the results of testing data will be shared with the participant’s legally authorized representative using secure means of communication between investigators and participants). A description of the data security in place to protect the confidentiality of the data is available. Study-stopping rules for the study are in place. The study will be stopped immediately if a serious adverse event that occurred is suspected to be related to the study.

## 9. Discussion

Pressure injuries are a complex and prevalent healthcare concern, particularly in community settings. Existing nutritional studies on PI wound healing have primarily focused on single-component interventions or hospital-based populations, often lacking individualized dietary support [17,19,20,22]. Recent trials have explored multi-component interventions but have shown statistically non-significant results [20,22]. This study addresses these gaps by implementing a comprehensive PI care bundle intervention, including education, dietetic support with medical nutritional supplements, and trained home care/community nurses in nutrition care. The primary objectives are to evaluate the clinical and cost-effectiveness of the intervention on PI-related outcomes. Considering the unique healthcare landscape, the focus on community settings in Singapore adds to the study’s significance.

To our knowledge, the INCA Trial is the first and largest trial attempting a complex intervention on PIs in a community setting. The INCA Trial falls under the category of effectiveness research [40]. Effectiveness research seeks to provide a comprehensive representation of the target study population cohort while contrasting novel interventions with standard clinical practices. Consequently, the findings will be instrumental in informing clinical judgments, thereby enhancing healthcare delivery’s quality, efficacy, and cost-effectiveness.

